## 6.5. Other evaluations

Pharmacological genomic studies, etc. are not included.

# Statistical analysis plan

## Determination of subject number

**Target number of subjects**: 106

The target number of subjects for each of the experimental and comparator groups of this study is 42. Considering a drop-out rate of 20%, this study will enroll 53 subjects per treatment arm (106 in total).

#### Rationale:

The purpose of this study is to show the non-inferiority of the gastroprotective effect of Naxozol in osteoarthritis patients compared to that of celecoxib, as evaluated by the average change in the LDQ (Leeds Dyspepsia Questionnaire) score from baseline after 12 weeks of oral administration.

In previous studies that evaluated the symptomatic improvement of gastrointestinal disorders with a Likert scale such as the LDQ, 0.40 was used as the minimal clinically important difference (MCID) in the degree of improvement.(30, 31, 32) Hence, the non-inferiority margin for this study was also set at 0.4. The LDQ consists of a 5-step Likert scale.

In a study by Holtmann et al. on the efficacy of Itopride in the improvement of functional dyspepsia, the standard deviation of the average change in the LDQ was 0.63 - 0.65. In this study, the standard deviation (σ) was set at 0.65 for a more conservative approach. (22)

With a power of 80% and a one-sided α of 0.025, the number of subjects per treatment arm, as estimated by the sample size derivation formula below, was 42. Considering a drop-out rate of 20%, this study will enroll 53 subjects per treatment arm (106 in total).

𝑛experimental

2

= 𝑛control =

[2𝜎2][𝑍_𝛼_

δ2

### + 𝑍_𝛽_]

[2 ∗ 0.652][1.96 + 0.842]2

= 0.42 ≅ 42

σ= standard deviation of change in LDQ

δ = non-inferiority margin

## Randomization

#### Screening number

All subjects will receive their own screening number regardless of randomization at the screening visit.

#### Randomization code generation

The randomization code will be generated for the subjects by the sponsor or sponsor’s proxy to evaluate the safety and efficacy of the investigational product. Randomization will be conducted before study commencement. The Permuted Block Randomization Method will be applied for each study site.

Allocation to each treatment arm is double-blinded, hence the investigator and subject cannot know which arm the subject is allocated to. The allocation proportion between the experimental drug and the comparator is 1:1.

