## Institution / principle investigator / subinvestigator / manager

## Institution

This study will be conducted in 10 institutions across Korea (for the institution names refer to: 12. Attachments). The list of institutions will be managed as a separate document to that of the protocol document.

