#### Subject allocation

Subject allocation is discussed in Section 4.4.2, and randomization is discussed in Section 7.2. After allocation, each subject is assigned a serial number that is used for their identification throughout the duration of the study. A serial number cannot be reused during the study. Stratification recruitment will not be conducted during the allocation. Subjects will be allocated to one of two groups in total: 53 in the experimental group and 53 in the control group.

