## Review of the study group allocation

This is a randomized study. In order to reduce bias from the investigator or subject during the safety and efficacy evaluation, this study was designed as a double-blind, randomized study. The randomized design will minimize the effect of baseline characteristics on the results of the study. (24) There will be no stratification during study group allocation.

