#### Subject allocation and randomization code maintenance

Subjects who fulfill the inclusion / exclusion criteria will be assigned randomization numbers in the order of study enrollment. Each subject will be assigned to a treatment arm according to the randomization number and will receive the appropriate investigational product.

The investigator and the subject cannot know whether the subject received the experimental drug or the comparator before study termination. After study termination, the sponsor will open the code to the investigator for data analysis.

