## Primary outcome analysis

Average change in LDQ from baseline after 12 weeks of oral administration of the investigational product: descriptive statistics (sample size, mean, standard deviation, median, min, max) will be presented for LDQ change after 12 weeks of investigational product administration in each treatment arm. To prove non-inferiority of the experimental drug, the one-sided 97.5% confidence interval for the between-group difference in LDQ change will be calculated. If the 97.5% upper confidence limit is smaller than the non-inferiority margin of 0.40, the null hypothesis is rejected, and non-inferiority is proven. Additionally, before investigational product administration, the total LDQ score will be categorized into three groups (No / Very Mild: 0-8; Mild / Moderate: 9-24; Severe / Very Severe: 25-40) for further analysis.

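### Section 7.2 randomises in permuted blocks within each site, yet Section 4.2.5 (and, less clearly, 4.1) says allocation is not stratified; one rule is needed, and 7.5.2 should state that the primary interval is adjusted for site

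*Protocol*

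**What the plan says.** Three places in the protocol describe how subjects are allocated.

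- Section 7.2, on generating the randomisation code: "The Permuted Block Randomization Method will be applied for each study site". The same section adds "The allocation proportion between the experimental drug and the comparator is 1:1" and has the code prepared before the study starts.
- Section 4.2.5: "There will be no stratification during study group allocation".
- Section 4.1, under subject allocation: "Stratification recruitment will not be conducted during the allocation". This passage also refers the reader to 7.2 for the randomisation itself.

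Two further passages bear on whether there is one list or one per site. Section 4.4.1 numbers randomised subjects serially within site. Section 7.2 says that eligible subjects "will be assigned randomization numbers in the order of study enrollment", without saying whether that order runs within site or across the trial. Section 1.3.1 gives the number of sites: "This study will be conducted in 10 institutions across Korea".

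For the primary analysis, Section 7.5.2 says only that "the one-sided 97.5% confidence interval for the between-group difference in LDQ change will be calculated" and that its upper limit is compared with the margin of 0.40. The synopsis says the same. Neither names a test, a model or a covariate, and site is neither included nor excluded.

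**The concern.** Blocks run separately at each site make site a stratum, so the list cannot be built as 7.2 describes and also be unstratified. With 106 subjects over 10 sites, the average is 106/10 = 10.6 per site. Ten site lists and one central list then give visibly different balance within sites. The code is prepared in advance and passed to the person who packages the drug (Section 5.8), so the choice is made once, early, and out of sight of the investigators.

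The allocation rule also bears on the analysis. Blocking within site takes differences between sites out of the treatment comparison. A pooled two-arm standard error leaves those differences in the error term, so its interval is somewhat too wide whenever LDQ change differs by site. What is at stake there is power, together with a decision about site adjustment that should not be left until the data have been seen.

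**Working it through.** **1. The text.** Permuted blocks for each site (7.2) means separate block sequences by site, which is stratification by site. No stratification during group allocation (4.2.5) denies this in plain words. Section 4.1 is weaker evidence: it speaks of stratification in connection with recruitment and defers to 7.2. The within-site numbering in 4.4.1 fits 7.2. The contradiction needs no assumption, and the surrounding text leans towards 7.2 as the intended scheme.

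**2. The plan's own sample size.** The inputs come from Section 7.1: margin 0.40, SD 0.65, one-sided alpha 0.025, power 80%, drop-out 20%.

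- n per arm = 2 × 0.65² × (1.96 + 0.842)² / 0.40² = 41.46, rounded up to 42.
- 42 / (1 − 0.20) = 52.5, rounded up to 53.

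Both figures reproduce. The formula is the plain two-sample one and contains no site term.

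**3. Interval half-width, exact balance within site.** Take 0.65 as the total SD. The within-site SD is then 0.65 × √(1 − ICC). The ICC is an assumption, because the protocol gives none.

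- Unadjusted: t(82 df) × 0.65 × √(2/42) = 0.282.
- Adjusted for 10 sites: t(73 df) × 0.65 × √(1 − ICC) × √(2/42). The degrees of freedom fall by 82 − 73 = 9.

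| ICC | Adjusted half-width | Change from 0.282 |
|---|---|---|
| 0 | 0.283 | +0.2% |
| 0.02 | 0.280 | −0.8% |
| 0.05 | 0.276 | −2.4% |
| 0.10 | 0.268 | −5.0% |
| 0.20 | 0.253 | −10.4% |

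**4. Simulation with drop-out.** Exact balance will not survive 20% drop-out, so the comparison was simulated. The set-up was 106 subjects over 10 sites with random site sizes, blocks of 4 within site (block size assumed), random 20% drop-out, and 5,000 trials per setting. The true difference was 0.40 for type I error and 0 for power. The pooled t-interval was compared with an interval from a model with fixed site effects.

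| ICC | Mean half-width, pooled / site-adjusted | Type I error, pooled / adjusted | Power, pooled / adjusted |
|---|---|---|---|
| 0 | 0.281 / 0.286 | 2.7% / 2.8% | 78.3% / 77.3% |
| 0.02 | 0.280 / 0.283 | 2.5% / 2.4% | 79.1% / 78.4% |
| 0.05 | 0.280 / 0.278 | 2.4% / 2.6% | 81.0% / 80.8% |
| 0.10 | 0.280 / 0.272 | 2.2% / 2.4% | 80.3% / 82.0% |
| 0.20 | 0.278 / 0.255 | 1.5% / 2.3% | 82.2% / 86.4% |

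The simulation standard error of a 2.5% rate is √(0.025 × 0.975 / 5,000) = 0.22 percentage points. The departure at ICC 0.20 is therefore clear, while the 2.2% at ICC 0.10 lies within about 1.4 standard errors of nominal.

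The power gain from adjustment is 82.0 − 80.3 = 1.7 points at ICC 0.10 and 86.4 − 82.2 = 4.2 points at 0.20. A normal-approximation formula suggests more (80.5% rising to 84.4% and 88.4%). It assumes perfect balance, ignores the lost degrees of freedom, and does not credit the pooled estimate with the stability that within-site blocking already gives it. The simulated gains are the ones to use.

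**The case against.** The best defence on the allocation rule is that only 7.2 says how the list is generated. Section 4.1 sends the reader there, so does the opening of Section 4.4, and the subject codes run within site. The 4.1 sentence may concern recruitment. The 4.2.5 sentence follows a remark about baseline characteristics, so it may mean only that patient factors are not used as strata. This makes 7.2 the likely intention. It does not remove the conflict, because 4.2.5 as written excludes any stratification.

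On the analysis, a reader might infer that the primary analysis leaves site out and that its interval is therefore too wide. The documents do not support either statement as fact. No model is named, and the interval in 7.5.2 could equally be site-adjusted. Model terms are commonly left to a statistical analysis plan, which is not shown here, so silence alone is no defect. A pooled analysis is suggested by the two-sample sample-size formula, by the two-sample t and Wilcoxon tests for continuous secondary outcomes in 7.5.3, and by the absence of site from 7.5, but it is not stated.

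A reader might also argue that the investigator-completed LDQ (Appendix 2) makes a site effect likely. The endpoint is a change from baseline, however, so a constant rating level at a site cancels. Only site differences in change matter, and nothing in the protocol shows how large those are.

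Finally, leaving site out errs on the safe side for a non-inferiority claim. That stands.

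**Conclusion.** The contradiction between 7.2 and 4.2.5 is certain, with 4.1 as weaker support, and it must be reconciled.

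The consequence for the analysis is conditional on two things: that the interval is computed without site, and that LDQ change varies by site. Under the simulation's assumptions (blocks of 4, random drop-out, ICC from 0 to 0.20), adjustment gains nothing or loses slightly at ICC 0 to 0.02 and is about neutral at 0.05. It gains about 2 points of power at 0.10 and about 4 at 0.20. Unadjusted type I error falls to about 2.2% and 1.5% at those last two values.

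A positive non-inferiority result is not threatened. The possible loss is modest, but the design starts from 80% power with 42 evaluable subjects per arm and has little to spare.

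**What to change.** State one allocation rule in 4.1, 4.2.5 and 7.2, for example: randomisation is stratified by site only, using permuted blocks within site. Make clear in 7.2 that the enrolment order used for randomisation numbers runs within site.

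Add to 7.5.2 that the primary interval is adjusted for site, as the randomisation stratum, with a rule for pooling very small sites fixed before unblinding.

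The cost is a change of wording and up to 9 degrees of freedom. If site explains almost nothing, the interval is slightly wider (0.286 against 0.281 in the simulation at ICC 0, with power about 1 point lower). The planned 42 evaluable and 53 enrolled per arm stay as they are.

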#### Subject allocation and randomization code maintenance

Subjects who fulfill the inclusion / exclusion criteria will be assigned randomization numbers in the order of study enrollment. Each subject will be assigned to a treatment arm according to the randomization number and will receive the appropriate investigational product.

The investigator and the subject cannot know whether the subject received the experimental drug or the comparator before study termination. After study termination, the sponsor will open the code to the investigator for data analysis.

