## Termination of study

In this study, Visit 3 is defined as the “end of study (trial) visit’, and subjects who have completed Visit 3 are defined as completed subjects. If the following situations occur, this study will not be deemed completed:

- - There are remaining subjects who are still due to receive investigational products.
  - The pre-specified visit schedule at a study site has not been completed.

If a subject misses a visit or is lost to follow-up despite reasonable requests for a visit, the corresponding subject will be deemed to have terminated the study participation. No further evaluation will be conducted after study termination.

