## Drugs or therapies contraindicated during study participation

Drugs other than investigational products, especially one of the drugs listed below, should not be administered during the study period, on principle:

1. NSAIDs (LDA [<325 mg/day low dose aspirin] excluded) other than investigational products.
2. Other gastroprotective drugs (H2 blockers, PPIs, misoprostol, etc.).
3. IV or oral corticosteroids (oral corticosteroids corresponding to ≤7.5 mg / day prednisone, topical ointments, eyedrops, nasal agents excluded).
4. Intraarticular or intramuscular corticosteroids or hyaluronic acid.
5. Glucosamine and / or chondroitin sulfate.
6. Lithium.
7. Antiretrovirals (atazanavir, atazanavir sulfate).

All drugs deemed necessary by the investigator, as per the investigator’s medical opinion, can be given. However, if a drug administered without an investigator’s assessment is deemed to have the capacity to influence the safety and efficacy evaluation of this study, the corresponding subject will be excluded from PP analysis. All drugs administered, and their dosage, route of administration, and reason for administration, must be recorded in a case report form signed by the investigator.

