## Blinding

- Confirmation of the inability to differentiate between the investigational products:

This study applies double-blinding to which of the experimental drug or the comparator is being administered. The investigational products for this study (experimental drug: Naxozol tablet; comparator: Celebrex capsule) differ in color and packaging, so this study is a double-placebo study that uses a placebo for the experimental drug that is equal in form, shape, and packaging to the experimental drug, and a different placebo for the comparator that is equal in form, shape, and packaging to the comparator, ensuring that the double-blinding of the investigator and subjects will be maintained during the study period. Neither the investigator nor the subject can be aware of whether the experimental drug or the comparator was administered to the subject until the termination of the study.

- Preparation and maintenance of the randomization code and unblinding envelope:

The randomization code will be created by the sponsor or a proxy randomization code generator designated by the sponsor. The generated randomization code will be sent to the person in charge of packaging the experimental drug and comparator for [name] (Department of Orthopedics, Severance Hospital). The unblinding envelope will be provided to the investigator in case emergency unblinding is necessary. The unblinding envelope will be safely sealed with the study arms for the study subjects until the time of unblinding. After the termination of the study, a monitoring agent will confirm that the unblinding envelope remains sealed.

- Collection of the investigational product:

The blind must be maintained until the time of unblinding. For this, the investigational products must be sealed and stored appropriately.

- Unblinding of the double-blind:

Neither the investigator nor the subject should know whether the experimental drug or the comparator was administered. After the termination of the study, the sponsor will open the code to the investigator for data analysis. The randomization code should not be accessed until uncoding, according to appropriate process after the termination of study. However, unblinding for the entire subject group or for individual subjects is possible for the evaluation of safety and efficacy by the investigator.

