#### Monitoring of a subject’s adverse event

The investigator must monitor and follow up a subject who has an adverse event that may be associated with the investigational product during the study period until disappearance of the said adverse event or confirmation of final progress, unless follow-up becomes impossible. The investigator must do due diligence to confirm the information regarding the adverse event and must document such information. The investigator is responsible for appropriate additional treatment and follow-up observation of the adverse event. The sponsor must actively follow up adverse events occurring during the study period and collect all relevant information. However, for SAEs, such measures must continue until the resolution of the SAE or confirmation of final progress, while for all other adverse events, such measures will only continue until database lock.

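### The randomization code may be opened to the investigators after study termination, and nothing in the protocol requires the database to be locked first

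*Protocol*

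**What the plan says.** Two sections of the protocol say when the code is released. Section 7.2, on subject allocation and code maintenance, says: "After study termination, the sponsor will open the code to the investigator for data analysis". Section 5.8 (Blinding) says the same: "After the termination of the study, the sponsor will open the code to the investigator for data analysis".

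Section 5.8 adds one restriction: "The randomization code should not be accessed until uncoding, according to appropriate process after the termination of study". The next sentence is introduced as an exception to it: "unblinding for the entire subject group or for individual subjects is possible for the evaluation of safety and efficacy by the investigator". That exception has no time limit and is not confined to emergencies.

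Section 4.9 (Termination of study) gives two situations in which the study does not yet count as completed: "There are remaining subjects who are still due to receive investigational products", and "The pre-specified visit schedule at a study site has not been completed". Both concern dosing and visits. Data cleaning and lock are not mentioned.

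Database lock comes up under the heading on monitoring of a subject's adverse event. Serious events are followed to resolution or a confirmed final course, "while for all other adverse events, such measures will only continue until database lock". That passage does not link lock to the code.

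**The concern.** A release rule should name the event after which no arm-sensitive judgement remains to be made. That event is normally database lock, with analysis-set membership already decided. The protocol names study termination instead, and the only completion criteria it offers can be met while data are still being gathered and corrected.

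Three kinds of decision could then be taken by people who know the arm:

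- causality and outcome of adverse events still open after the last visit, which feed the between-arm comparison of drug-related events;
- corrections to case report forms;
- any per-protocol decisions not yet settled. The per-protocol set is one of the two sets in which the primary endpoint is analysed.

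Section 1.4 appoints no data safety monitoring committee, so the protocol places no independent blinded body between the investigators and these judgements.

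**Working it through.** The point is procedural. No figure in the plan depends on it, and the sample size (42 evaluable and 53 enrolled per arm) is unaffected. The check is to set the relevant sections side by side.

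**1. When may the code be opened?** After study termination (5.8, 7.2), for data analysis, by a process that 5.8 does not describe. Separately, 5.8 allows whole-group or individual unblinding for evaluation by the investigator at no stated time. Section 5.9 restricts the unblinding envelope to emergencies, so the exception in 5.8 is also wider than 5.9.

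**2. Can data still be open then?** Yes.
- The section defining the adverse event reporting period has events continuing at the end-of-study visit monitored until they improve or stabilise.
- The section on monitoring adverse events runs non-serious follow-up to database lock and serious follow-up to resolution or confirmed final course.
- Section 9.1 has the investigator make and countersign form changes, each dated. It sets no cut-off relative to the code.

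**3. Which decisions are exposed?**

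| Item | When it is obtained or decided | Exposed? |
| --- | --- | --- |
| LDQ score | Visit 3 (6.1) | No |
| Return of unused product | Visit 3 (6.1) | No |
| Most form entries and causality ratings | Form completion, a listed Visit 3 task (6.1) | Mostly no |
| Causality and outcome of events open after Visit 3 | Later, no date given | Yes |
| Form corrections | No cut-off (9.1) | Yes |
| Allowance for lost or damaged product in compliance | No date given (7.5.3) | Possibly |
| Concomitant drug that "is deemed to have the capacity to influence the safety and efficacy evaluation of this study" | No date, no named decision-maker (5.3.3) | Possibly |
| Serious violation by sponsor or investigator assessment | Mostly during treatment (4.5.1) | Residual cases only |

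**4. Does this reach the primary error rate?** Let A be the event that the full analysis set meets the 0.40 margin and B the event that the per-protocol set does. Section 7.4 defines the full analysis set by randomization, dosing and at least one efficacy evaluation, so a late per-protocol exclusion does not change it. With the true difference at the margin and the full-analysis test holding its one-sided 0.025 level,

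P(A and B) ≤ P(A) = 0.025.

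If both sets must succeed, late per-protocol exclusions cannot raise the false non-inferiority rate above the nominal level.

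**The case against.** The strongest reply is that the order of lock, blinded review and set sign-off belongs in the SAP or the data-management documents, which are not shown. If the protocol were silent, that would settle the matter. It is not silent: it states a release trigger twice and adds a whole-group exception. A SAP requiring lock first would be adding a condition that the protocol's own rule lacks.

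A second reply is that release for data analysis, by an appropriate process, implies clean data. That is a fair reading, and it is why the text cannot be said to order early opening. But neither phrase names lock or a blinded review, and the whole-group exception that follows weakens the protective reading.

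A third reply is that most judgements are made by Visit 3, form changes are dated and countersigned, and the records are open to monitoring and audit. This stands, and it narrows the exposure to the later items in the table.

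A reader might go further and infer that section 4.9 fixes termination at the last visit. It does not: it lists when the study is not complete and gives no positive definition of termination.

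A reader might also infer that unblinded per-protocol exclusions would inflate the type I error of the non-inferiority claim. That would require deliberate removal of the worst outcomes from one arm and a claim resting on the per-protocol set alone. The documents support neither: the Synopsis makes both sets main analyses, and excluded subjects remain in the full analysis set.

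**Conclusion.** The point holds as a defect in the release rule. Sections 5.8 and 7.2 allow investigators to hold the code before lock, while adverse-event follow-up and form amendments can continue. What is at risk is the blinded status of late causality and outcome assessments, of form corrections and of residual per-protocol decisions. LDQ assessment is not at risk, and no inflation of the primary type I error is shown.

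The size cannot be given as a number, because the documents do not say how many events or set decisions would be open after Visit 3.

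The conclusion on the primary test rests on two assumptions. The first is that both sets must succeed. The Synopsis and 7.5.1 point that way without stating it as a rule. The second is that the exclusions in 4.5.1 bear on the per-protocol set and leave the full analysis set as 7.4 defines it; the parenthesis in 4.5.1 is unclear on this.

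**What to change.** Replace the release sentence in both 5.8 and 7.2 with wording such as:

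*Apart from emergency unblinding under section 5.9, the code is opened only after all queries are closed, causality assessments are final, each subject's Safety, FA and PP membership has been signed off blind, and the database is locked.*

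In 5.8, delete the exception for whole-group or individual unblinding, or make it subject to the same condition. Serious events unresolved at lock can still be followed as the adverse-event section already provides, with the causality rating held at lock used for analysis.

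The cost is a few sentences and later access to the code, by the length of the data-cleaning period, which the documents do not give. No visit, subject or analysis is added, and emergency unblinding is unchanged.
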